#### Procedure

Women with PCOS and healthy control women will be asked to participate in the study and will be given an informational brochure. A week later a coordinator will contact each woman by telephone to give further information about the study, to answer questions, to check eligibility, and to determine participation. If a woman wants to participate, written informed consent will have to be provided. Only then peripheral venous blood samples will be collected (if not already recently done). After this the participant will receive an e-mail with a link to the web-based questionnaires. The questionnaires will also be available on paper if necessary. Within 2 weeks an appointment will be made to conduct the sexual response assessment (VPA) (Figure 1).

**Figure 1 fig1:**
[figure not shown]
(A) Flowchart design protocol assessments. (B) Order of tasks and stimuli during VPA measurement. PCOS = polycystic ovary syndrome; VPA = vaginal pulse amplitude.

The sexual response assessment will be performed at the psychophysiological laboratory of LUMC or AMC. All women will be tested individually by a trained female experimenter. The experimenter will explain the details of the experimental procedure and the purpose of the experiment. The experimenter will then leave the room to allow the participant to apply the vibrator and insert the vaginal probe privately. The participant is allowed to put on her clothes again after applying the vibrator and inserting the vaginal probe. During the experimental procedure the experimenter will be in an adjacent room; contact will be possible by using an intercom. All further instructions, the stimuli, and the questionnaire about self-reported sexual arousal and affect will be presented on a monitor in the participant's room. At the end of the experiment, an exit interview questionnaire will be administered. Participants will be asked about their reactions to the experimental procedure and the use of the genital device (Figure 1).

### Statistical Analysis

Normality of the outcome data will be determined with Shapiro-Wilk tests. In case of non-normality, an appropriate transformation will be performed. The difference between women with PCOS and controls will be analyzed with separate multilevel regression analyses for each of the 5 outcomes. Independent variables will be PCOS (vs controls), fantasy (vs film), and vibration and interactions of PCOS with fantasy and vibration. *P* values of .01 will be considered significant.

For the differences between women with PCOS and controls, and women using OCPs and women not using OCPs, OCP use and interactions with PCOS, fantasy, and vibration will be added to the multilevel analyses.

Mediation regression analyses, as described by Mathieu and Tailor,^129^ will be extended to multilevel mediation regression analyses to estimate the mediating effects of steroid hormone levels, and sexual and psychosocial parameters in the relation of PCOS/OCP use on the 5 sexual outcome measures.

We will apply regression curve estimation with sexual function as the dependent variable and CAG repeat length and several functions of the CAG repeat length as independent variables to analyze a possible non-linear relation.

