Genital response will be measured using a vaginal photoplethysmograph assessing VPA.^122^, ^123^, ^124^ VPA is a sensitive, specific, and reliable measure of changes in vaginal vasocongestion in response to sexual stimulation^125^ and has been used in earlier studies in women with gynecological or neurological diseases.^120^^,^^126^ The vaginal device is sized and shaped as a vaginal tampon and can easily be inserted by the participant herself. It contains a light source and an optical sensor. The light source illuminates the capillary bed of the vaginal wall and the sensor responds to the light backscattered by the vaginal wall and the blood circulating within it. When the signal is connected to an alternating current amplifier, VPA is measured, which reflects the phasic changes in vaginal engorgement accompanying each heartbeat, with larger amplitudes reflecting higher levels of vaginal vasocongestion. Genital responses will be recorded continuously during the experiment. VPA will be averaged for the baseline condition and each erotic stimulus, and for each stimulus condition a change from the baseline score will be calculated. Ratings of self-reported sexual arousal and affect will be collected after each erotic stimulus. Participants will be asked to assess on a 7-point Likert scale their strongest feeling of sexual arousal.^127^^,^^128^

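### The normality rule tests raw outcomes instead of model residuals; it misfires for the 7-point arousal rating and leaves the scale of the stimulus interactions open for the two laboratory outcomes

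*Protocol article*

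**What the plan says.** All of this is in the protocol article.

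- Statistical Analysis sets the check and its consequence: "Normality of the outcome data will be determined with Shapiro-Wilk tests. In case of non-normality, an appropriate transformation will be performed". The level of the test and the transformation are not named.
- The same section then plans "separate multilevel regression analyses for each of the 5 outcomes", and specifies: "Independent variables will be PCOS (vs controls), fantasy (vs film), and vibration and interactions of PCOS with fantasy and vibration". P values of .01 count as significant.
- Sexual Response Assessment describes the subjective outcome: "Participants will be asked to assess on a 7-point Likert scale their strongest feeling of sexual arousal". It is repeated: "Ratings of self-reported sexual arousal and affect will be collected after each erotic stimulus". There are four stimuli, so each woman contributes four ratings.
- For VPA, the same section says that "for each stimulus condition a change from the baseline score will be calculated".
- Table 1 lists genital and subjective responsiveness among the five primary outcomes, with FSFI, FSDS-R and SDI.
- Sample Size Calculation gives 67 women per group, driven by the SDI at d = 0.60.

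**The concern.** Three things do not fit together.

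1. The test is aimed at the raw outcome. A regression model allows the outcome to differ in mean between groups and stimuli. The pooled raw data are then a mixture, which can look non-normal although the model is correct. Sexual Response Assessment itself expects larger genital responses to visual stimuli than to fantasy or vibration.
2. A single item with seven possible values is discrete. Shapiro-Wilk reacts to the ties, and no one-to-one transformation removes ties. For this outcome the rule calls for a remedy that cannot meet its own criterion.
3. Interactions depend on the scale. If a non-linear transformation is chosen after the data have been tested, the PCOS by fantasy and PCOS by vibration terms answer a different question from the one on the original scale.

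At stake is the analysis scale of two of the five primary outcomes, and with it the meaning of their interaction terms.

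**Working it through.** **Planned size.** With d = 0.60, two-sided alpha 0.05/5 = 0.01 and power 0.80, the two-sample t-test needs 66.56, so 67 per group and 134 in all. This reproduces the protocol's figure. The checks below use 67 per group.

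**Assumptions.** The article gives no distribution, mean or SD for the rating or for VPA by stimulus, and no level for Shapiro-Wilk. These are assumed below and varied where possible.

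**(a) 7-point rating.** Ratings were simulated as a normal variable rounded to whole numbers and clipped to 1 to 7, with means 3 to 5 and SDs 1 to 2.

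| Data tested | Rejected at 5% | Rejected at 1% |
|---|---|---|
| One stimulus, n = 67 | 100% | 92% to 100% |
| One stimulus, n = 134 | 100% | 100% |
| Four stimuli pooled, 134 × 4 = 536 rows | 100% | not run |
| n = 134 after log, square root or square | 100% | not run |
| n = 134 after rank-based normal scores | 100% | 100% |

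A mean over the four stimuli fails much less often (18%), but a model with stimulus terms does not use that mean.

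**(b) VPA pooled over stimuli, exactly normal errors.** Inputs: 134 women, four equally spaced stimulus means, within-woman correlation about 0.5, Shapiro-Wilk at 5%.

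| Spacing of stimulus means | Raw outcome rejected | Residuals from cell means rejected |
|---|---|---|
| 0.25 to 0.5 SD | about 5% to 8% | about 8% to 11% |
| 1 SD | about 40% | about 8% to 11% |

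Uneven means push the raw figure higher: 68% for means of 0, 0, 2 and 2 SD, and 88% to 100% for two wider patterns. The residual rate exceeds 5% because the four rows of one woman are correlated, whereas Shapiro-Wilk assumes independent values. A formal test on residuals would therefore not be a clean replacement.

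**(c) Questionnaires.** FSFI, FSDS-R and SDI give one score per woman and have no stimulus factor. With normal errors and a group shift of d = 0.6, Shapiro-Wilk on the pooled raw scores rejects in about 5%, its nominal rate.

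**(d) Scale of the interaction.** Take illustrative means of 2 and 4 for controls under two stimuli, and 1.5 and 3 for PCOS.

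- Raw scale: (3 − 1.5) − (4 − 2) = −0.5.
- Log scale: ln(3/1.5) − ln(4/2) = 0.

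In simulation with 67 per group, alpha 0.01 and assumed SDs, data without interaction on the log scale were significant on the raw scale in 51% of runs. Data without interaction on the raw scale were significant on the log scale in 86%. These runs used positive values, so they illustrate the principle and do not forecast VPA.

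**(e) Is a transformation needed for the rating?** An untransformed t-test of the 7-point item at 67 per group has a type I error of 0.009 to 0.011 at the 0.01 level. This covers a two-group comparison, not the full multilevel model.

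**(f) What is lost by never transforming.** For a log-normal outcome shifted by 0.6 SD on the log scale, with 67 per group and alpha 0.01, power is 74% untransformed at a log-SD of 0.5, 63% at 0.8 and about 52% at 1.0. After a log transformation it is about 80% throughout.

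**The case against.** Checking normality and transforming if needed is conventional, and a condensed article may leave the choice of transformation, residual diagnostics and sensitivity models to an analysis plan. That stands as regards missing detail. It does not cover a rule that the article does state and that names the outcome data as its target.

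Several stronger readings are tempting, and the documents do not support them.

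- *The rule damages all five primary outcomes.* A reader might point to the d = 1.9 and 2.3 in Sample Size Calculation, where raw-data rejection is about 10% and 30% with normal errors. Those values compare women with and without sexual problems, not PCOS with controls. At d = 0.6 the effect vanishes.
- *VPA will usually be sent for transformation.* This depends on stimulus means that the article does not give. The article also does not say that data are pooled over stimuli for the test, and testing within cells would remove the mixture.
- *Change scores can be negative, so transformation is impossible.* Negative values rule out a plain log or square root. The article asks only for an appropriate transformation, and some accept negative values (cube root, inverse hyperbolic sine, Yeo-Johnson).
- *Transformation gains nothing and can simply be banned.* Check (f) shows a real loss of power on the raw scale when an outcome is strongly skewed.
- *The PCOS comparison itself is invalid.* No inflation of its type I error has been shown. The primary aim is the PCOS-control difference, and the stimulus-specific hypothesis in the Background concerns androgen level rather than PCOS status. The interactions matter because the model tests them, not because they are the whole primary aim.

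**Conclusion.** The point holds for the two laboratory outcomes. For the per-stimulus arousal rating, failure of the test is practically certain at the planned size under every distribution tried. It is an empirical near-certainty, not a logical necessity, and it persists at 134 women after a transformation designed to normalise. For VPA, the raw-data test can flag a correct model, but how often ranges from the nominal rate to almost always, depending on the assumed stimulus means. For both outcomes, an unnamed non-linear transformation chosen from the data leaves the scale of the PCOS by fantasy and PCOS by vibration terms open. A linear rescaling would not. FSFI, FSDS-R and SDI are barely touched.

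A reader might infer that a wrong primary conclusion is likely. That is not demonstrated. This is a rule that should be reworded before analysis, not a flaw that undermines the design.

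**What to change.** In Statistical Analysis:

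1. Replace the Shapiro-Wilk test on raw outcomes with a graphical check of the residuals of the fitted multilevel model.
2. Analyse the 7-point rating on its original scale, with robust or bootstrap standard errors clustered by woman. Add an ordinal mixed model as a sensitivity analysis.
3. Name the VPA scale in advance: either the raw change from baseline or one stated transformation that accepts negative values. Report the other as a sensitivity analysis.

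The cost is a little more analysis work, and some power if the raw scale is chosen for an outcome that proves strongly skewed. That trade-off is the reason to settle the VPA scale deliberately beforehand, for example from the research group's previous VPA data. Sample size and alpha stay as they are.

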We expect to find lower sexual function and higher sexual distress in the PCOS group compared with the control group.^38^ Further, we expect to find stronger genital and self-reported sexual responsiveness in women with higher androgen levels in both the fantasy and vibrotactile stimulation conditions but not with visual sexual stimuli.^99^^,^^100^

Following the threshold model,^64^, ^65^, ^66^, ^67^, ^68^, ^69^, ^70^, ^71^ we do not predict a linear relationship between VPA response and androgen levels (free testosterone and total testosterone). We do expect women with the lowest bioavailable androgen levels (control women using OCPs) to show lower levels of VPA response than women in the upper 3 quartiles of bioavailable androgen levels (women with PCOS not using OCPs).

We hypothesize that women with PCOS will score lower on various psychosocial and mental health measures compared with control women.^17^ We expect these scores to be associated with impaired scores on sexual function questionnaires.^34^, ^35^, ^36^, ^37^

We have no specific expectation for the relationship between sexual outcomes and CAG repeat length in both women with and without PCOS. CAG repeat length will be measured to exploratively assess individual differences in sensitivity to androgens and the relationship with PCOS status and other variables.

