#### Sexual Response Assessment

Sexual response will be assessed in 4 erotic stimulus conditions: 3-minute self-induced erotic fantasy, 2-minute vibrotactile glans clitoris stimulation, 5-minute erotic film, and 5-minute vibrotactile glans clitoris stimulation combined with an erotic film.^116^^,^^117^ Both erotic films depict heterosexual foreplay and intercourse. This film material has been previously used in studies from the same research group.^116^^,^^118^, ^119^, ^120^, ^121^ The short clips are taken from women friendly erotic films which are known to be effective in inducing a genital response. During the erotic fantasy condition, participants will be asked to fantasize about a pleasant sexual situation. The vibrotactile glans clitoris stimulation is provided by a small hands-off vibrator (2-cm diameter), attached to lycra panties. Vibrotactile glans clitoris stimulation has been used previously in studies on sexual response in women, and is known to elicit genital and subjective sexual arousal.^121^ The intensity of the vibration can be varied from very low^1^ to high.^10^ In the present study, high-intensity vibration will be provided. Each stimulus period is preceded by a 5-minute neutral film period, and followed by a 10-minute return-to-baseline interval during which participants will work on a non-erotic concentration task and watch a neutral film. A computer program coordinates the administration of the films and the vibrotactile glans clitoris stimulation.

All participants will go through the different stimulus conditions in the same order. Because sexual responses to erotic fantasy and vibrotactile glans clitoris stimulation are expected to differ according to androgen status, these 2 stimulus conditions are presented first, to avoid carry over from the visual stimuli that are known to be androgen independent and to elicit higher genital responses than fantasy and vibrotactile glans clitoris stimulation.^61^^,^^99^^,^^100^

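### For the two laboratory outcomes, the stated model gives four stimulus conditions only two stimulus terms and does not name the contrast that tests the group difference

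*Protocol article*

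**What the plan says.** The Sexual Response Assessment section sets out the session: "Sexual response will be assessed in 4 erotic stimulus conditions: 3-minute self-induced erotic fantasy, 2-minute vibrotactile glans clitoris stimulation, 5-minute erotic film", and as the fourth condition "5-minute vibrotactile glans clitoris stimulation combined with an erotic film". VPA is scored condition by condition: "for each stimulus condition a change from the baseline score will be calculated". Self-reported arousal is likewise rated after each stimulus. Each woman therefore contributes four values to each of the two laboratory outcomes.

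The Statistical Analysis section plans "separate multilevel regression analyses for each of the 5 outcomes" and lists the fixed effects: "Independent variables will be PCOS (vs controls), fantasy (vs film), and vibration and interactions of PCOS with fantasy and vibration". It sets the significance level at .01. It gives no coding for the stimulus terms and names no coefficient or contrast as the test of the group difference. The extension to OCP use adds interactions with the same two stimulus terms.

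The Background makes the PCOS-control difference on each outcome the primary aim. It also predicts that women with higher androgen levels respond more strongly "in both the fantasy and vibrotactile stimulation conditions but not with visual sexual stimuli". The Sexual Response Assessment section refers to "visual stimuli that are known to be androgen independent" and adds that these stimuli produce higher genital responses than fantasy or vibration.

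**The concern.** The list of independent variables does not match the design it is meant to analyse. Four conditions need three condition terms, and the article gives two. Some restriction is therefore imposed on the condition means, and the same restriction is imposed on the PCOS effects through the interactions.

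On the most natural reading, the restriction merges vibration alone with film plus vibration. The design keeps these apart: one contains the visual stimulus and the other does not, they last 5 and 2 minutes, and fantasy and vibration come first so that film does not carry over into them.

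A second question is which number answers the primary aim. Once PCOS interacts with the stimulus terms, the meaning of the PCOS coefficient depends on how those terms are coded. If the coding and contrast are not fixed before the data are seen, two of the five primary tests at the .01 level can be defined afterwards.

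**Working it through.** **Inputs.** Four conditions and one score per condition (Sexual Response Assessment); two stimulus terms, each interacting with PCOS (Statistical Analysis); two-sided alpha 0.01, power 0.80, 67 per group, VPA effect d = 0.66 (Sample Size Calculation). Assumed, because the article does not give them: the within-woman correlation ρ between conditions (0.3, 0.5, 0.7), equal variances, and the pattern of PCOS effects across conditions.

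**The plan's own figures.** Alpha = 0.05/5 = 0.01. For the SDI, d = 0.60 with a t-test gives 66.56, so 67 per group as stated. For VPA, n² = 0.10 gives d = 2·√(0.10/0.90) = 0.667, and n = 2·3.417²/0.667² rounds up to 53 as stated. The total of 134/0.9 = 149 agrees with the stated 150. None of this depends on the point below.

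**Counting terms.** Within each group the model has an intercept, fantasy and vibration: 3 parameters for 4 means. The matrix of these terms over the four conditions has rank 3 under every coding tried, so one degree of freedom is always missing.

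**What each coding implies.** Let δF, δV, δM and δMV be the PCOS-control differences in fantasy, vibration alone, film, and film plus vibration. With balanced data and a woman-level random intercept, the PCOS coefficient weights them as follows:

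| Coding | Distinct rows | δF | δV | δM | δMV |
|---|---|---|---|---|---|
| A: 0/1, fantasy = 1 only in fantasy | 3 | 0 | 0 | 1 | 0 |
| B: 0/1, fantasy = 1 in both no-film conditions | 4 | 0.25 | −0.25 | 0.75 | 0.25 |
| C: fantasy +1, both film conditions −1, vibration alone 0 | 4 | 0.5 | 0 | 0.5 | 0 |
| D: factorial, ±0.5 | 4 | 0.25 | 0.25 | 0.25 | 0.25 |
| E: A, mean-centred | 3 | 0.25 | 0.25 | 0.25 | 0.25 |

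A and E pool the two vibration conditions. B and D avoid pooling by counting vibration alone as fantasy and assuming that vibration adds the same amount with and without film. C imposes another linear restriction.

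**Coding A in detail.** PCOS = δM. PCOS × fantasy = δF − δM. PCOS × vibration = (δV + δMV)/2 − δM. The overall difference can still be recovered: PCOS + 0.25·(PCOS × fantasy) + 0.5·(PCOS × vibration) = 0.25·(δF + δV + δM + δMV).

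**Power for the group difference**, 67 per group, alpha 0.01. The variance of the four-condition mean is (1 + 3ρ)/4 of a single condition's.

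| Assumed pattern | Film-only coefficient | Four-condition mean, ρ = 0.3 / 0.5 / 0.7 |
|---|---|---|
| d = 0.66 in all four | 0.893 | 0.998 / 0.988 / 0.961 |
| 0 in film, 0.66 in the other three | 0.01 | 0.943 / 0.853 / 0.751 |
| 0 in both film conditions, 0.66 in fantasy and vibration alone | 0.01 | 0.578 / 0.437 / 0.342 |

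The entries of 0.01 are the rejection rate when the true film difference is zero.

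**Power for the vibration interaction under coding A.** Take vibration alone minus film as having 80% power, so z = 2.576 + 0.842 = 3.417 before rounding. Its variance is proportional to 2(1 − ρ). That of the pooled version is proportional to 1.5(1 − ρ), so ρ cancels.
- No PCOS effect in film plus vibration: the estimate is halved. The ratio is (0.5/√1.5)/(1/√2) = 0.577, z = 1.97, power Φ(1.97 − 2.576) = 0.27.
- Same PCOS effect in both vibration conditions: the ratio is √(2/1.5) = 1.155, z = 3.95, power Φ(3.95 − 2.576), about 0.91.

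**The case against.** A reader might infer that, for the laboratory outcomes, the PCOS P value tests film alone. The article does not establish this. It needs both 0/1 coding with film as reference and the bare PCOS coefficient read as the test, and neither is stated. Centred coding gives the overall difference directly, and coding A yields it as a contrast. Coding and contrasts are often left to a fuller analysis plan.

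A reader might also infer that the vibration hypothesis cannot be tested, or that its power falls to 27%. That figure assumes no PCOS effect in film plus vibration, which the article never predicts for a condition that includes vibration. If the effect is in both vibration conditions, pooling raises power to about 91%. The Background prediction is by androgen level, not PCOS status. PCOS can be diagnosed without hyperandrogenism, about half of each group is to use OCPs, and hormone levels enter through the mediation models. Calling film androgen independent does not rule out a PCOS effect there through body image, mood, self-esteem or BMI.

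Finally, only two of five primary outcomes are touched, and the average over four conditions is itself a choice that can have low power, as the third pattern shows.

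All of this limits the consequences. It does not supply the missing condition term. The article did list its independent variables, and the list does not fit four conditions under any coding.

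**Conclusion.** The point holds for VPA and self-reported arousal. The stated model is one condition term short in each group, whatever the coding. On the plain 0/1 reading, vibration alone and film plus vibration share one mean and one PCOS effect, against the article's own expectation that visual stimuli give higher genital responses than vibration. The article also leaves open which quantity tests the group difference. Film alone is one possible outcome of that gap, not a demonstrated one.

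Stimulus terms cannot apply to the FSFI, FSDS-R and SDI, so the single model description is wrong for those three as written, although without the terms their PCOS coefficient is simply the group difference.

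The size is conditional. For d = 0.66 in every condition, power is 0.893 for film alone against 0.961 to 0.998 for the average. For the vibration interaction, pooling can lower power from 80% to 27% or raise it to 91%. These figures rest on assumed effects, and those for the average also on assumed correlations. Planned recruitment does not change.

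**What to change.** For VPA and self-reported arousal, enter condition as a four-level factor with PCOS × condition (3 df) and a woman-level random effect. Name the PCOS difference averaged over the four conditions as the test of the group difference. Name PCOS × (fantasy minus film) and PCOS × (vibration alone minus film) as contrasts. Use the same condition factor where OCP use is added. Fit the FSFI, FSDS-R and SDI without stimulus terms.

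The cost is a reworded paragraph and two extra parameters in the primary model: one condition term and its PCOS interaction. No new data are needed. If the PCOS effect is in fact the same in both vibration conditions, the vibration contrast loses some power compared with pooling (80% instead of about 91% in the illustration). The wording should be fixed before the laboratory outcomes are analysed.

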#### Questionnaires

We will measure the following variables as primary outcomes (Table 1): sexual function with the FSFI total score (19 items, cutoff <26.55 indicative of sexual dysfunction)^101^; sexual distress with the FSDS-R total score (13 items, score >15 indicative of distress)^101^; and solitary and dyadic sexual desire with the SDI (14 items, 2 scales [solitary desire scale and dyadic desire scale] and total scale; a higher score reflects higher levels of sexual desire)^102^ as an additional measure of sexual desire due to limitations in the desire scale of the FSFI.^103^

**Table 1 tbl1:** Overview of primary and secondary outcome measures and independent variables

Outcome measures
Primary
Female Sexual Function Index
Female Sexual Distress Scale-Revised
Sexual Desire Inventory
VPA: genital sexual responsiveness
VPA: subjective sexual responsiveness
Secondary (mediators)
Sexual Esteem Scale
Rosenberg Self-esteem Scale
Body Image Self-consciousness Scale
The Multidimensional Body-Self-Relations Questionnaire-Appearance Scales
Hospital Anxiety and Depression Scale
Secondary (moderators)
Sexual and Physical Abuse Questionnaire
Sexual Excitation/Sexual Inhibition Inventory for Women
Revised Dyadic Adjustment Scale
Independent variables
PCOS status
OCP use

OCP = oral contraceptive pill; PCOS = polycystic ovary syndrome; VPA = vaginal pulse amplitude.

Other variables will be used as mediators (Table 1): sexual self-esteem measured by Sexual Esteem Scale (10 items, a higher total score indicates more sexual self-esteem)^49^^,^^104^; general self-esteem with the Rosenberg Self-Esteem Scale total score (10 items, a higher total score indicates more positive self-esteem)^105^, ^106^, ^107^; body self-consciousness with the Body Image Self-Consciousness Scale total score (15 items, a higher total score indicates greater body self-consciousness)^49^^,^^108^; body image with the Multidimensional Body-Self-Relations Questionnaire-Appearance Scales subscale (34 items, a higher total score indicates a more positive body image)^109^; and mental health with the Hospital Anxiety and Depression Scale total score (14 items, a higher total score indicates mental complaints).^110^^,^^111^

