Some variables will be used as moderators (Table 1) as they are not caused by the independent variable (PCOS status): a history of sexual and physical abuse measured with Sexual and Physical Abuse Questionnaire (7 items, yes/no answers)^112^; sexual excitation and sexual inhibition propensity by Sexual Excitation/Sexual Inhibition Inventory for Women (36 items, 2 subscales, low Sexual Excitation Scale indicates low excitation, high Sexual Inhibition Scale indicates high inhibition)^113^; relationship satisfaction by Revised Dyadic Adjustment Scale total score (14 items, cutoff >48 for no distress).^114^^,^^115^

All questionnaires have been validated and will be available in a secure online environment.

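### Three declared moderators enter no stated model, and the stated mediation models carry no covariates, so the mediator-to-outcome paths are open to confounding by abuse history, which is already collected

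*Protocol article*

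**What the plan says.** Under Questionnaires, Table 1 has a class headed "Secondary (moderators", separate from the secondary mediators. The text gives the reason: "Some variables will be used as moderators (Table 1) as they are not caused by the independent variable (PCOS status". Three instruments follow:

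- "a history of sexual and physical abuse measured with Sexual and Physical Abuse Questionnaire (7 items, yes/no answers"
- "sexual excitation and sexual inhibition propensity by Sexual Excitation/Sexual Inhibition Inventory for Women"
- "relationship satisfaction by Revised Dyadic Adjustment Scale total score (14 items, cutoff >48 for no distress"

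Statistical Analysis then describes four sets of models.

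1. The main multilevel models: "Independent variables will be PCOS (vs controls), fantasy (vs film), and vibration and interactions of PCOS with fantasy and vibration".
2. The same models with OCP use and its interactions with PCOS, fantasy and vibration.
3. Multilevel mediation models for "the mediating effects of steroid hormone levels, and sexual and psychosocial parameters in the relation of PCOS/OCP use" on the five sexual outcomes.
4. Curve estimation for CAG repeat length.

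No covariate is named for the mediation models. Mediation is one of the secondary aims given in the Background. Apart from PCOS by OCP use, no moderation question appears among the aims.

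**The concern.** Two gaps meet here.

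The first is a mismatch within the article: three instruments are given a role, and the list of regressors contains no term that carries it out.

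The second matters more for interpretation. Attributing part of a PCOS difference to self-esteem, body image or mood requires that the mediator and the outcome share no uncontrolled cause. The design does not secure this. The study is observational and the controls are age-matched only. Participant Recruitment and Selection draws controls from advertisements, flyers and a volunteer pool, while the Discussion reports that recruitment of cases worked well through patient support groups and poorly through the expertise center. A history of abuse could plausibly lower self-esteem, body image and mood and also impair sexual function. The authors treat it as not caused by PCOS, so on their own premise adjusting for it removes no part of a PCOS effect. Left out, it could make a psychosocial scale look like a route from PCOS to sexual function when the two merely share a cause.

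**Working it through.** **Comparison of roles and models**

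| Declared moderator | Main models | OCP models | Mediation models | CAG models |
|---|---|---|---|---|
| Abuse history | not named | not named | not named | not named |
| Sexual excitation/inhibition | not named | not named | not named | not named |
| Relationship satisfaction | not named | not named | not named | not named |

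None of the three is named in any stated model.

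**The plan's own figure**

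From Sample Size Calculation: d = 0.60, two-sided alpha 0.05/5 = 0.01, power 0.80. The two-sample t test needs 66.6, so 67 per group and 134 in total, as stated. With 10% dropout, 134/0.9 = 148.9, so 149; the article rounds to 150. The figure is sound and concerns main effects only. N = 134 and alpha .01 are carried forward.

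**False-positive rate on the mediator-to-outcome path**

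Assumptions: one common cause, correlated r1 with the mediator and r2 with the outcome; no true effect of mediator on outcome; PCOS group in the model; one outcome value per woman. The documents give neither r1 nor r2.

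- Spurious standardised path: b = r1 × r2.
- Residual df: 134 − 3 = 131; critical t = 2.61.
- Noncentrality: b × √(131/(1 − b²)).

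| r1 / r2 | b | Noncentrality | Rate by formula | Simulated, cause omitted | Simulated, cause adjusted |
|---|---|---|---|---|---|
| 0.2 / 0.3 | 0.06 | 0.69 | 3% | 3% | about 1% |
| 0.3 / 0.4 | 0.12 | 1.38 | 11% | 11% | about 1% |
| 0.4 / 0.5 | 0.20 | 2.34 | 39% | 40% | about 1% |

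The simulation used 6,000 replicates per cell. If either correlation is zero, b = 0 and there is no inflation.

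**From that path to a spurious indirect effect**

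A false indirect effect also needs PCOS to shift the mediator. With 67 per group at alpha .01, power for that path is 19% at d = 0.3, 39% at d = 0.4 and 80% at d = 0.6 (assumed shifts); with no shift it is 1%. Requiring both paths to be significant, and treating the two tests as independent, the middle row becomes:

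- no shift: 0.113 × 0.01 = 0.1%
- d = 0.3: 0.113 × 0.195 = 2%
- d = 0.4: 0.113 × 0.386 = 4%
- d = 0.6: 0.113 × 0.803 = 9%

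**Power of the moderator tests, if they are stated**

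Assumptions: outcome SD 1, 67 per group, moderator distributed equally in both groups.

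- Binary moderator with prevalence p: SE = √[(2/67)(1/p + 1/(1 − p))]. At p = 0.5, SE = 0.346, the detectable difference in group effect is (2.576 + 0.842) × 0.346 = 1.18 SD, and power for a 0.60 SD interaction is 20%. At p = 0.1, SE = 0.576, the detectable difference is 1.97 SD and power is 6%.
- Continuous moderator: SE = √(2/67) = 0.173, and the detectable slope difference is 3.418 × 0.173 = 0.59 SD per SD.

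**The case against.** **The article is condensed.** The full protocol and any analysis plan are not shown and may contain the missing terms. A reader might infer that moderation will never be tested; the article does not support that. What stands is narrower: it lists its regressors explicitly and assigns these instruments a role, and the two do not meet.

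**A moderator is not by definition a confounder.** A reader might infer that the mediation estimates are confounded. Bias needs an effect on both mediator and outcome, and no section states one or reports an imbalance in abuse history between arms. This stands: it is a plausible risk of unknown size, not an established bias.

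**The mediators are already separated from the moderators.** A reader might take the phrase about sexual and psychosocial parameters as drawing the moderators in as mediators, particularly since the Discussion cites the Revised Dyadic Adjustment Scale as a psychosocial measure. Table 1 points the other way: its mediator list holds a sexual scale and several psychosocial ones, which fits the phrase. A cross-reference is enough.

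**The simulated rates cover one path.** Reading 40% as the chance of a false mediation finding would be wrong, because a shift of the mediator by PCOS is also needed. This stands.

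**Adjusting for excitation/inhibition could do harm.** The Background says androgens are thought to sensitise brain and genitals to sexual stimuli, so excitation may lie downstream of hormones, and it overlaps with the desire and arousal outcomes. This stands and keeps it out of the main mediation model.

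**The moderation tests would be weak.** True, and a reason to label them exploratory.

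**Conclusion.** The point holds in limited form. The article declares three moderators and states no model that uses them, and its stated mediation models name no covariates. The mediator-to-outcome paths are therefore open to confounding by variables the study already collects.

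The size cannot be read from the documents. Under assumed correlations from 0.2/0.3 to 0.4/0.5, the false-positive rate for that one path is about 3% to 40% against a nominal 1%. The rate for a full indirect effect is lower: in the middle case, 0.1% to 9%, depending on how far PCOS shifts the mediator. These figures assume a single common cause, one outcome value per woman and, for the combined rates, independent tests of the two paths.

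The matter affects a secondary aim. It leaves the primary comparison of women with and without PCOS untouched. It is worth acting on because the remedy is nearly free.

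**What to change.** In Statistical Analysis:

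1. Add abuse history as a covariate in both the mediator and the outcome equations of the mediation analyses. Add a sensitivity analysis that also includes sexual excitation/inhibition; keep that scale out of the main mediation model because it may be downstream of androgens and overlaps with the outcomes.
2. Tie the sexual and psychosocial parameters in the mediation sentence to the mediators listed in Table 1.
3. State the PCOS-by-moderator terms for all three instruments, including relationship satisfaction, entered one at a time and labelled exploratory with low power.

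All scales are already collected, so the change is to wording and analysis code only. The downside is a few more parameters and a few low-power exploratory tests.
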